#### Data management {19}

The lead researcher will be responsible for all data collection.

Data entry will be conducted by the lead researcher and by the independent video observers who are annotating the video data. The latter will use the Noldus ObserverXT software to watch and annotate videos and then store their observation files on the secure School of Food Science and Nutrition server.

#### Data security

Data will be stored securely in a limited access folder in the drive for the School of Food Science and Nutrition. Data will also be backed up on an external hard drive. Some video and audio data will be shared with commercial companies who develop analysis software we plan to use. Data sharing agreements and protocols will be added to this DMP as they are completed.

Please see the OASES dynamic Data Management Plan at ISRCTN: 40249947, for up-to-date data management information.

#### Confidentiality {27}

All video data collected will be stored securely on-site at the school where it is collected, on a dedicated external hard drive, and will remain property of the school until released to the University of Leeds for use in the study. Video data will only be released to the University of Leeds after opt-in caregiver consent is obtained for a given child. The child’s video data will then be copied to another external hard drive, which will be stored securely at the University of Leeds, School of Food Science and Nutrition. Anonymous participant ID numbers will replace names in labelling participant profiles/data. All data will be stored securely, under physical locking or password protection, on secure University of Leeds servers.

#### Plans for collection, laboratory evaluation and storage of biological specimens for genetic or molecular analysis in this trial/future use {33}

See the “Additional consent provisions for collection and use of participant data and biological specimens {26b}” section; there will be no biological specimens collected (Fig. 4).

**Fig. 4 Fig4:**
[figure not shown]
SPRIIT schedule of enrolment, interventions, and assessments

### Statistical methods

#### Statistical methods for primary and secondary outcomes {20a}

For each participant, pre/post-intervention difference will be calculated for each primary measure, plus the normalised sum of primary measures (to represent overall ‘curiosity and confidence’). Each set of data will be analysed using regression models with pre-post difference as the outcome. Secondary measures will be examined using the same methods as primary measures. The number of clusters is too small to analyse using a multi-level model, however school and class will be included as a covariate.

For each participant, data will be collected at baseline and follow-up. The main outcomes (dependent variables) will be individual scores in WTT, enjoyment/engagement (from facial expression), and verbal engagement at follow-up. The difference in scores between the intervention and the control group will be calculated for each of the primary measures, plus an overall score consisting of the sum of primary measures which represents overall curiosity and confidence. Each set of data will be analysed using two level regression models (where appropriate), to take into account the clustering of children within schools. The analysis will be adjusted for baseline scores.

The intervention should benefit those children most in need of support. To reflect this in our analysis, we will split the participants into three sub-groups according to their score on a given measure at baseline (low, mid, high). Each grouping will cover 1/3 of the range for that measure. It is important that any benefits be observed in the low and/or mid groups and not just be driven primarily by the high group. High scores are considered desirable in all measures.

The liking secondary measure will be examined using the same regression methods.

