### Outcomes {12}

The observational scenario is a tasting activity done in small groups (see the “Plans for assessment and collection of outcomes {18a}” section). The test activity will conducted < 6 weeks before (baseline) and < 6 weeks after intervention delivery is completed. Analysis metric for all measures is follow-up scores, adjusted for baseline, for all children.

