### Sample size {14}

There is no perfectly comparable study upon which to base our sample size estimates, as our behavioural measures and study design are novel to the domain. Using a similar testing method in a younger age group (1–3 year olds), Dazeley and Houston-Price [31] reported that out of 4 foods (2 fruits, 2 vegetables) offered to nursery school children, the mean number of foods tried was 1.44 with a standard deviation of 1.38. To measure mean increases of 0.5 (the equivalent of 50% of children eating one more food), using the same standard deviation found by Dazeley and Houston Price, a sample size of 160 children is needed in each arm (control and intervention) to provide 90% power. We will aim to recruit 400+ children, but recruitment may be challenging due to ongoing pandemic COVID-19 conditions.

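### The primary analysis is defined both as a pre-post difference and as follow-up adjusted for baseline, and the protocol does not say which governs

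*Protocol article*

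**What the plan says.** The section Statistical methods for primary and secondary outcomes {20a} gives two accounts of the main analysis.

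- **First paragraph.** "Each set of data will be analysed using regression models with pre-post difference as the outcome". It then says "The number of clusters is too small to analyse using a multi-level model, however school and class will be included as a covariate". Baseline score is not listed as a covariate here, nor among the control variables in the additional analyses section {20b}.
- **Second paragraph.** "The main outcomes (dependent variables) will be individual scores in WTT, enjoyment/engagement (from facial expression), and verbal engagement at follow-up". It adds "Each set of data will be analysed using two level regression models (where appropriate), to take into account the clustering of children within schools" and "The analysis will be adjusted for baseline scores".

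Outcomes {12} sides with the second account: "Analysis metric for all measures is follow-up scores, adjusted for baseline, for all children".

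The same split appears in the FaceReader material. The description of the validation speaks of pre-post differences, while the list of validation questions speaks of follow-up adjusted for baseline. The exploratory liking analysis inherits the ambiguity, because it borrows the method used for the primary measures.

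**The concern.** The two accounts name different dependent variables for the same primary measures and the same composite. Neither is labelled primary, sensitivity or superseded. This is not detail deferred to an analysis plan: the article states two rules, and an analyst could follow either and claim that it was prespecified.

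Read as written, the first model is a change-score comparison without baseline adjustment and the second is an analysis of covariance. These weight the baseline differently, so they generally give different estimates and standard errors from the same data. Whole classes are randomised, so some chance imbalance at baseline is to be expected. What is at stake is precision, and the freedom to pick the version that reaches significance.

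**Working it through.** **Inputs.** From Sample size {14}: the target ("To measure mean increases of 0.5"), the spread ("the mean number of foods tried was 1.44 with a standard deviation of 1.38"), 160 children per arm and 90% power. Assumed, because the protocol does not give them: two-sided alpha 0.05, equal SDs at baseline and follow-up, and a baseline to follow-up correlation r of 0.3 to 0.7. All figures are at individual level and ignore clustering unless stated.

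**Step 1, the plan's own figure.** n per arm = 2 × (1.960 + 1.282)² × 1.38² / 0.5² ≈ 160.1, which rounds up to 161 against 160 stated. Power at 160 per arm is 0.8999. The figure is reproduced. The SD is that of a raw score.

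**Step 2, residual variance in units of SD².** The unadjusted difference has 2(1-r). Follow-up adjusted for baseline has 1-r². The ratio is 2(1-r)/[(1-r)(1+r)] = 2/(1+r).

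| Assumed r | Difference | Adjusted | Ratio | n per arm for 90% power (difference / adjusted) | Power at 160 per arm (difference / adjusted) |
|---|---|---|---|---|---|
| 0.3 | 1.40 | 0.91 | 1.54 | 225 / 146 | 78.2% / 92.5% |
| 0.5 | 1.00 | 0.75 | 1.33 | 161 / 121 | 90.0% / 96.3% |
| 0.7 | 0.60 | 0.51 | 1.18 | 97 / 82 | 98.7% / 99.5% |

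The stated 160 per arm therefore matches an unadjusted change-score analysis only if r is about 0.5.

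**Step 3, point estimates in one trial.** Let Dy and Db be the arm differences at follow-up and baseline. The change-score estimate is Dy - Db. The adjusted estimate is Dy - r × Db. They differ in size by (1-r) × Db. With r = 0.5 and an assumed imbalance of 0.3 foods, the gap is 0.5 × 0.3 = 0.15 foods, or 30% of the 0.5 target.

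**Step 4, how likely that imbalance is.** The SE of Db is 1.38 × √(2/160) = 0.154, so 0.3 is about 1.9 SE and is reached or exceeded in roughly 5% of trials without clustering. Assuming an intraclass correlation of 0.05 and 25 children per class, the design effect is 1 + 24 × 0.05 = 2.2. The SE becomes 0.154 × √2.2 ≈ 0.23 and the chance about 19%.

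**Step 5, significance.** At r = 0.5 and 160 per arm the SE is 1.38 × √1.00 × √(2/160) = 0.154 for the difference and 1.38 × √0.75 × √(2/160) = 0.134 for the adjusted score. The 5% thresholds are 1.96 × 0.154 = 0.30 and 1.96 × 0.134 = 0.26. Even with no imbalance, an estimate between these two values is significant under one model only.

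**Step 6, simulation.** In 3,000 individually randomised trials (160 per arm, r = 0.5, true effect 0.5), the mean estimates were 0.496 (difference) and 0.497 (adjusted), so neither is biased. The empirical SEs were 0.1542 and 0.1338, a variance ratio of 1.33 as in step 2. The two estimates differed by 0.06 on average and by 0.31 at most.

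**Step 7, the reading under which they agree.** If baseline B is a covariate in both models, Y - B = a + b·arm + (c-1)·B is the same equation as Y = a + b·arm + c·B, so b is identical. The simulation confirmed this to 5 × 10⁻¹⁵.

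**The case against.** The strongest reply is that the protocol already leans one way. Outcomes {12} fixes the metric for all measures as follow-up adjusted for baseline, the second paragraph of {20a} repeats it, and the FaceReader validation questions use the same form. If the sentence on baseline adjustment was meant to cover both paragraphs, the treatment estimates coincide and only wording is at issue. This stands in part. It shows which version to keep, but the first paragraph is not withdrawn and does not itself mention baseline, so the conflict remains.

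Three stronger readings are tempting and are not supported.

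- **Bias.** A reader might infer that the change score is biased by regression to the mean. Under randomisation both estimators are unbiased; the (1-r) term is a shift conditional on the imbalance observed in a given trial.
- **Ceiling.** A reader might infer that the pilot finding of about 77% of children tasting 7 to 9 samples singles out the change score. A ceiling affects a linear baseline-adjusted model too. The weighted willingness-to-taste score also multiplies the tasted proportion by a 1 to 5 Gusto rating, and no ceiling is reported for the facial or verbal measures.
- **Sign.** A reader might infer that the two analyses could point in opposite directions. That needs an effect near zero; a shift of 0.15 does not reverse an effect of 0.5.

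It is also fair to say that the magnitude rests on assumptions. The protocol gives no r and no intraclass correlation. Different food sets before and after make a low r plausible but do not establish it. Pairing classes within school limits imbalance between schools. The 0.5-food scale comes from a four-food study of younger children.

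**Conclusion.** The point holds. Current text in {20a} defines the primary analysis in two conflicting ways, and no rule says which decides. The conflict has numerical consequences only if the difference model omits baseline, which is how the first paragraph reads. In that case the cost is precision: a variance ratio of 2/(1+r), or 1.54, 1.33 and 1.18 at assumed r of 0.3, 0.5 and 0.7, at individual level with equal SDs. Estimates from a single trial also separate by (1-r) times the chance baseline imbalance. The realistic risk is that statistical significance depends on which version is chosen once the data are seen. The figures in foods are illustrative, because the weighted primary score is not measured in foods. The contradiction itself does not depend on any of these assumptions.

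**What to change.** In {20a}, replace the sentence that makes the pre-post difference the outcome with one primary model for every primary measure and for the composite: the follow-up score regressed on arm, with that measure's own baseline as covariate, as Outcomes {12} already states. Keep the pre-post difference for description only. Align the FaceReader wording with this.

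Do not simply delete the rest of the first paragraph. It also says that there are too few clusters for a multi-level model and names school and class as covariates, while the second paragraph specifies two-level models for children within schools. Deletion would settle that second conflict by default. Participant timeline {13} randomises class groups in pairs within school, so the same edit should name one method that accounts for randomisation by class. Entering class as fixed indicators cannot be that method, because arm is then a linear combination of them: with 10 illustrative classes, the design matrix has rank 10 with or without arm.

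The cost is a text amendment and one explicit decision on the clustering method. No extra data collection or recruitment is needed.

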**Methods:**

Four hundred plus children from 4+ schools will either complete the Flavour School programme (experimental group) or have no intervention with normal school teaching (control group), cluster-randomised within-schools, by school class. Baseline data collection will consist of video recorded behavioural observation during a tasting activity, and post-intervention data collection will repeat this activity after the experimental group have completed the intervention. Process measures will be assessed using a teacher engagement feedback questionnaire.

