### Participant timeline {13}

The trial runs over the 2021–2022 school year. Schools nominate eligible year groups for participation. Cluster randomisation will be at the level of paired teaching class groups, within-school. For example, a school chooses year 1 to participate. Year 1 contains two classes, 1A and 1B. At random, class 1A is assigned to the control group and 1B to the experimental group. See Fig. 1. Schools can choose the timing of intervention delivery separately for each pair of classes. Therefore, different class pairs can have different intervention timings.

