#### Methods for additional analyses (e.g. subgroup analyses) {20b}

At the individual level, we will control for any effects of sex, age, and Pupil Premium^2^ eligibility. At the group level, we will control for any effects of school and school class group. Any group differences will be interpreted in the light of information about process adherence and teacher engagement, as reflected in the teacher survey (see Additional file 1: Appendix 3).

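### Classes are randomised, but neither planned analysis treats the class as the cluster: one makes the arm effect inestimable, the other understates its standard error

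*Protocol article*

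**What the plan says.** **Unit of randomisation.** The abstract describes the trial as "cluster-randomised within-schools, by school class". Participant timeline {13} says the same: "Cluster randomisation will be at the level of paired teaching class groups, within-school". Its example reads: "At random, class 1A is assigned to the control group and 1B to the experimental group". Each class therefore has one arm, and each school contains both.

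**First analysis.** The opening paragraph of Statistical methods for primary and secondary outcomes {20a} uses a change score: "Each set of data will be analysed using regression models with pre-post difference as the outcome". It then rules out a multi-level model: "The number of clusters is too small to analyse using a multi-level model, however school and class will be included as a covariate".

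**Second analysis.** The next paragraph of the same section takes the follow-up score adjusted for baseline and says: "Each set of data will be analysed using two level regression models (where appropriate), to take into account the clustering of children within schools".

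**Additional analyses.** Section {20b} adds: "At the group level, we will control for any effects of school and school class group". The list of independent measures names arm, school and school class together.

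Nowhere does the protocol specify a random effect for class, standard errors clustered on class, or an analysis of class-level summaries.

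**The concern.** The two paragraphs of {20a} contradict each other on whether a multi-level model is used at all, and on whether the outcome is a change score or a baseline-adjusted follow-up score. Choosing either one does not solve the problem, because each mishandles the class. Entering class as a covariate absorbs the comparison the trial exists to make. Clustering on school accounts for a level at which nothing was randomised and ignores the level at which it was.

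Every primary measure, the composite and the exploratory liking measure use these models. If the choice between versions stays open until the data are seen, it could also be guided by the results.

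**Working it through.** **Inputs from the protocol.** Class is the randomised unit, paired within school (abstract; {13}). Five schools are named in Study setting {9}, and the abstract says four or more. The recruitment target is 400 or more children, and the sample size rests on a difference of 0.5 foods, SD 1.38 and 90% power ({14}).

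**Assumptions, not in the protocol.** Children analysed per class (m), number of class pairs, and class-level ICC within school. Each is shown over a range.

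**1. The plan's own figure.** Taking two-sided alpha of 0.05, n per arm = 2 × [1.38 × (1.960 + 1.282) / 0.5]² = 160.08. This reproduces the stated 160. It is an individual-level calculation with no ICC or design effect.

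**2. First analysis: class as a fixed covariate.** For child i, arm = the sum, over intervention classes k, of the indicator that child i is in class k. Arm is therefore a linear combination of the class indicators whatever the ICC or layout. Ranks of the design matrix with intercept, arm, school and class indicators:

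| Layout | Columns | Rank with arm | Rank without arm |
|---|---|---|---|
| 4 schools, 16 classes | 20 | 16 | 16 |
| 5 schools, 20 classes | 25 | 20 | 20 |
| 5 schools, 10 classes | 15 | 10 | 10 |

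Adding arm never raises the rank. Software will either drop arm or drop another class indicator, and in the second case the printed arm coefficient depends on which one was dropped.

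**3. Second analysis: clustering on school only.** Write C for the class variance within school, E for the child variance and P for the number of pairs, so that ICC = C / (C + E).

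- True variance of the arm contrast: 2(C + E/m) / P. The school effect cancels because both arms sit in each school.
- Variance the school-only model reports, approximately: 2(C + E) / (mP).
- Ratio of true to reported: (mC + E) / (C + E) = 1 + (m − 1) × ICC.

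The false-positive rate of a nominal 5% test is then about 2 × [1 − Φ(1.96 / √(1 + (m − 1) × ICC))]. For m = 25 and ICC 0.05 the ratio is 1 + 24 × 0.05 = 2.20, its root is 1.48, and the rate is 18.6%.

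| m | ICC 0.01 | ICC 0.02 | ICC 0.05 | ICC 0.10 |
|---|---|---|---|---|
| 10 | 6.0% | 7.1% | 10.4% | 15.5% |
| 15 | 6.6% | 8.3% | 13.3% | 20.6% |
| 20 | 7.2% | 9.5% | 16.0% | 25.0% |
| 25 | 7.8% | 10.7% | 18.6% | 28.8% |

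**4. Simulation.** No true effect, 4,000 runs per setting, regression on arm and school against a t-test on within-pair differences in class means:

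| Layout | Class ICC | School-adjusted | Paired class means |
|---|---|---|---|
| 4 schools, 8 pairs, m = 25 | 0 | 5.0% | 5.0% |
| | 0.02 | 11.6% | 4.7% |
| | 0.05 | 18.9% | 4.7% |
| | 0.10 | 28.5% | 4.4% |
| 5 schools, 10 pairs, m = 20 | 0 | 5.7% | 5.2% |
| | 0.02 | 9.9% | 4.9% |
| | 0.05 | 16.1% | 4.8% |
| | 0.10 | 26.3% | 4.6% |

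A further layout of 5 schools, 8 pairs and m = 25 gave 10.9%, 18.9% and 29.2% at ICC 0.02, 0.05 and 0.10, against 4.9–5.2% for paired class means. Simulation and formula agree. These runs used school as a fixed effect and did not adjust for baseline.

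**The case against.** Four points can fairly be made for the plan.

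- **Inestimability depends on how class is entered.** It requires class as a fixed categorical term; a random class term would be estimable, and the wording of {20b} alone could allow one. That is true of {20b}. But the sentence in {20a} that adds class as a covariate is the one that rejects a multi-level model, so the fixed reading is the natural one there.
- **The first paragraph may be leftover text.** Outcomes {12} gives baseline-adjusted follow-up as the metric for all measures, which matches the second paragraph. If so, the second analysis is the live one and still clusters on the wrong level. Its qualifier, that two-level models apply where appropriate, does not help: the only alternative on the page is the first analysis.
- **The inflation needs a positive class ICC, and none is given.** This stands. Zero is unlikely on the protocol's own account, however: teachers deliver the programme to whole classes, food sets are counterbalanced by class, and children are tested at shared tables of three or four ({18a}).
- **Twenty to 25 analysed children per class may be too many.** Only children with caregiver consent contribute data, and those without follow-up are excluded. Smaller classes give less inflation, as the table shows, and baseline adjustment may lower the residual ICC. This changes the size of the error, not its direction.

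**Conclusion.** The concern holds. The two paragraphs of {20a} cannot both be followed, and neither gives a valid analysis of a class-randomised trial. Under the first, with class as a fixed covariate, the arm effect is not estimable; this is algebra and rests on no assumed figure. Under the second, standard errors are too small whenever outcomes vary between classes within a school. With 20 to 25 children per class, the reported standard error is 0.82–0.85 of the true one at ICC 0.02, 0.67–0.72 at 0.05 and 0.54–0.59 at 0.10. The size depends on an ICC and a class size that the protocol does not give. With 10 to 15 children per class the false-positive rate would be about 7–8%, 10–13% and 16–21% at the same ICCs. This should be corrected before allocation is unblinded.

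**What to change.** Remove class as a covariate from {20a} and {20b}, and replace both paragraphs of {20a} with a single analysis. Model the follow-up score on arm, baseline score, age, sex and Pupil Premium eligibility, with the pair as actually randomised as a fixed stratum and class as a random intercept. Use a small-sample correction such as Kenward-Roger. A two-stage analysis is an equally acceptable choice: covariate-adjusted class means compared within pairs by a t-test. Name one of the two as primary. Define the stratum by the recorded pair, since year group is given only as an example in {13}.

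**Cost.** The change is to wording and uses data already planned. Intervals widen by the factor √(1 + (m − 1) × ICC): with 20 to 25 children per class, by 1.17–1.22 at ICC 0.02, 1.40–1.48 at 0.05 and 1.70–1.84 at 0.10. Degrees of freedom fall to about pairs minus one, for example 7 with eight pairs, or 4 if each of the five named schools supplied one pair.

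Power for 0.5 foods with 200 children per arm, by normal approximation without baseline adjustment, is 95% if clustering is ignored. It becomes 85–87%, 69–74% and 50–57% at those ICCs, before any loss from few degrees of freedom. That cost comes from the design; the present wording only hides it.

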### Behaviour patterns expected, based on pilots

We piloted the Flavour Explorers data collection scenario with over 200 children across the target age group and across three schools. During pilots of the evaluation methods (*with no intervention*), we observed variety in children’s engagement with the Flavour Explorers activity. Most children (~77%) tasted most or all samples (7–9). A large minority (~20%) of children were more cautious, tasting 1–6 items. A small minority of children (~2%) were very reluctant and tasted zero items.^3^

There were large differences in the gusto with which children tasted. Some gingerly licked or nibbled the samples, leaving most of each sample, whilst others consumed everything available. Some children were business-like, working their way through the samples with neither great reluctance nor great enthusiasm, perhaps a bit like completing any given piece of work at school. Others were quite animated, with multiple episodes of happy, fearful, disgust and surprise expressions. Disliking some samples often did not appear much of a barrier to tasting other samples. Children often found fun in disliking foods. Engaging in the activity can produce strong negative-valence facial expressions, for example when tasting sour or disliked foods.

We were concerned that children’s attention would be excessively drawn to the cameras filming them. However, in practice during piloting, such interest was mostly confined to the beginning and end of the sessions, with the Flavour Explorers activity mostly keeping the children engaged such that they appeared to forget about or ignore the cameras.

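### Equal-width baseline thirds put about 77% of children in the high group on self-report willingness-to-taste, so a benefit equal in all children could look driven by that group through size alone

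*Protocol article*

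**What the plan says.** The section Statistical methods for primary and secondary outcomes {20a} says that the intervention should help the children who most need support. It forms three groups from the baseline score on each measure and fixes their boundaries: "Each grouping will cover 1/3 of the range for that measure". These are bands of equal width, not of equal numbers of children. The section then attaches a condition for interpretation: "It is important that any benefits be observed in the low and/or mid groups and not just be driven primarily by the high group".

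The Discussion section Behaviour patterns expected, based on pilots reports how many of the nine foods children tasted with no intervention:
- "Most children (~77%) tasted most or all samples", defined there as 7–9 foods;
- "A large minority (~20%) of children were more cautious, tasting 1–6 items";
- "A small minority of children (~2%) were very reluctant and tasted zero items".

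The section Willingness-to-taste (WTT) defines self-report WTT as the proportion of the nine foods tasted. It defines WTT as that proportion multiplied by a Gusto rating from 1 to 5, and says that both will be reported.

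**The concern.** The condition asks where along the baseline scale the benefit lies. Comparing bands answers that fairly only if each band can show an effect of the same size about equally well. On self-report WTT the pilot shows scores piled up at the top, so equal-width bands must be very unequal in number. The group the protocol does not want to drive the result then has most of the precision, and the groups in which it wants to see benefit have little.

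At stake is the statement about children most in need. A programme that helped all children equally could be described as helping mainly those who already taste nearly everything. A chance result in the smaller groups could equally be taken as reassurance. The overall comparison of arms is not affected.

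**Working it through.** **Inputs**
- Effect 0.5 foods, SD 1.38, 160 per arm for 90% power, target of 400+ children: Sample size {14}. The SD comes from children aged 1–3 offered four foods.
- Pilot shares of about 77%, 20% and 2%: Behaviour patterns expected, based on pilots. They sum to 99%, so the share below 7 foods is 22% (20 + 2) or 23% (100 − 77).
- Assumed: two-sided alpha 0.05 (not stated), equal split between arms within each group, no allowance for clustering.

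**Reproducing the plan's figure**

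n per arm = 2 × (1.96 + 1.2816)² × (1.38/0.5)² = 2 × 10.507 × 7.618 = 160.1. This agrees with the stated 160. One-sided 0.05 would give 131, so two-sided is the reading that fits.

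**Group sizes on self-report WTT**

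Thirds of 0–9 foods are 0–3, 4–6 and 7–9. A child tasting exactly 6 sits on the upper cut and is counted here as mid; counting that child as high would only raise the high share. The pilot included children who tasted none and children who tasted all, so possible and observed range coincide.
- High: 0.77 × 400 = 308, or 154 per arm.
- Low and mid together: 0.22 × 400 = 88 to 0.23 × 400 = 92, or 44–46 per arm.
- Low alone: the pilot merges 1–6 foods, so the share lies between 2% (8 children) and 22% (88 children). An even spread over 1–6 would give 2% + 10% = 12% (48 children), but that is an assumption.

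**Power for 0.5 foods**

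Power = Φ(0.5 / (1.38 × √(2/n)) − 1.96), with n per arm.

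| Group | n per arm | Power |
|---|---|---|
| High | 154 | Φ(3.179 − 1.96) = 0.89 |
| Low and mid, 22% | 44 | Φ(1.699 − 1.96) = 0.40 |
| Low and mid, 23% | 46 | Φ(1.738 − 1.96) = 0.41 |
| Low alone, bounds | 4 to 44 | 0.07 to 0.40 |

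At 320 children (160 per arm), the high group has power 0.81 and low and mid pooled has 0.33–0.34. Clustering would lower all of these.

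**What an equal effect would look like**

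If the bands were judged by significance, the chance that high reaches it and low plus mid does not is about 0.89 × (1 − 0.40) = 0.53, treating the groups as independent. Whatever the effect and SD, if the SD is the same in both groups, the interval in low plus mid is √(308/92) = 1.83 to √(308/88) = 1.87 times as wide as in high.

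**Other measures**

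Gusto-weighted WTT runs from 0 to 5, with cuts at 1.67 and 3.33. Nine foods at Gusto 3 scores 3.0 (mid), and seven foods at Gusto 2 scores 7/9 × 2 = 1.56 (low). The 77% therefore does not carry over. Under assumed Gusto distributions, independent of foods tasted, the high share ranged from about 12% to 41%. The protocol gives no distribution for Gusto or for the facial, verbal or composite measures.

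**The case against.** The strongest reply is that the imbalance is shown for one reported version of one measure only. That stands. A reader might infer that every measure puts most children in the high group. The documents do not support this: the pilot counts foods tasted and nothing else, and on the weighted score the high group may be a minority.

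A reader might also infer that a nearly empty low group must carry the condition alone. The wording is low and/or mid, so the relevant pool is the 22–23%, which is weak but not empty. The size of the low group cannot be derived beyond the 2–22% bounds. Nor can one argue from a low cut at −0.67 on the Enjoyment scale, because the primary facial measure adds Engagement to Enjoyment and so has a different range.

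The power figures borrow an SD and an effect from a different task and age group, and neither is established for children selected on baseline. Children already tasting 7–9 foods can gain at most two, so an equal effect in all children is an illustration, not a forecast. Both points stand; the contrast in precision depends on neither the SD value nor the effect size.

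The condition is worded as a caution, without a significance threshold, and how the bands are modelled may be set out in an analysis plan not shown. That limits the consequences but leaves the stated band rule as it is. Fixed cuts do have a merit: low keeps an absolute meaning. Equal-count thirds would not be better here, since with about 77% at 7–9 foods the upper two thirds, and part of the lowest, would consist of such children.

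**Conclusion.** The concern holds for self-report WTT and for the low and mid groups pooled. On the pilot figures about 77% of children fall in the high third, against 22–23% in the other two. Power for the plan's own effect is about 0.89 against 0.40–0.41 at 400 children, before clustering. Comparing bands this unequal cannot separate a benefit concentrated in the high group from one spread evenly. This rests on the main trial resembling the pilot, on two-sided alpha 0.05, and on the borrowed SD and effect. No share is claimed for any other measure. The change is worth making because the protocol's statement about children most in need depends on this rule, but the main comparison of arms does not.

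**What to change.** Base the statement about children most in need on an arm by continuous-baseline interaction in the baseline-adjusted model for each measure. Report the estimated effect with its 95% CI at prespecified low baseline values (for self-report WTT, for example 3 and 6 of nine foods) and at the median. This uses all children, needs no definition of range, and addresses directly whether benefit depends on baseline. Lower-quartile and median reporting points alone would not serve for self-report WTT, because with only 22–23% below 7 foods both fall among children tasting 7–9.

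The range bands may stay as descriptive display, with group sizes shown and no conclusion drawn from which band reaches significance.

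The cost is one extra model term, revised wording and an assumed form for the interaction, which the ceiling at nine foods makes worth checking. Intervals at low baseline values may still be wide, but the report would then show that openly.
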